### Recruitment {15}

To reach an adequate sample size, recruitment of participants is performed by different pediatric specialists from both the Urology and Pediatric Nephrology Department during the consultations. We chose to include patients who have not been treated yet with non-conservative therapies, among others to increase the number of potential participants. Additionally, treatment-naïve patients are easier to convince to participate in a sham-controlled trial than patients who have been unsuccessfully treated and want the guarantee of an effective treatment.

## Assignment of interventions: allocation

### Sequence generation {16a}

The randomization sequence list was computer-generated using the online platform “Sealed envelope” (available at: sealedenveloppe.com). Randomization is generated with a parallel 1:1 allocation of two treatment groups A and B, using random block sizes of 4. No stratification of participant characteristics was implemented.

Independently from the randomization sequence list, the physiotherapist defined randomly groups A and B (TTNS or sham).

Subsequently, the randomization sequence list was exempted for use to the physiotherapist.

### Concealment mechanism {16b}

The allocation sequence is not concealed for the physiotherapist, who assigns and implements the interventions. From the moment a participant is sent for a first visit to the physiotherapist, she allocates a number to the participant in order of appearance. The sequentially numbered participants will receive the treatment as indicated in the order of the randomization sequence list.

The research assistant, however, who analyzes all the data, is neither aware of the participant number, the group allocation per participant, nor of the identification of group A and B.

### Implementation {16c}

Participants will be enrolled by the PS or the research assistant. Afterwards, the allocation sequence is generated by coincidence. The participant schedules an appointment with the physiotherapist according to his or hers own preference in time and the availability of the physiotherapist. This sequence will determine the sequentially numbered list who is developed by the physiotherapist. Assignment of participants to interventions is also performed by the latter.

## Assignment of interventions: blinding

### Who will be blinded {17a}

The treatment is blinded for the patient, the parent, the treating PS, and the research assistant. The physiotherapist is the only unblinded party.

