### Trial design {8}

A prospective, single-center randomized controlled double-blinded trial is set up, comparing TTNS versus sham therapy. Participants are allocated on a 1:1 ratio to either the intervention arm, either or the control arm, according to a computer-generated list of random numbers. Superiority of TTNS over sham will be assessed.

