### Study schedule

For a structured overview of the study schedule, see Fig. 2 and Table 1. After enrolment, the participant is referred to the physiotherapist for a first visit (t_1_). Urotherapy and a first neuromodulation session are given. After home-therapy for 6 weeks, a second evaluation visit at the physiotherapist is planned (t_2_). Together with the parent and participant, the progression in symptoms is evaluated by review of the completed diaries. After the second 6-week period of home-therapy, a third follow-up visit at the physiotherapist is planned (t_3_). Primary outcomes are collected and delivered to the research assistant. At this point (at 12 weeks), the degree of clinical response to the treatment will be assessed. “No response” is defined as less than 50% increase in the average voided volume (AVV) compared to baseline, registered in the bladder diary. “Partial response” is predefined as 50–99% increase in the AVV, and “Complete response” as a 100% increase in AVV [10].

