### Strategies to improve adherence to interventions {11c}

At the first study visit, extensive counseling of the importance of therapy compliance is given to the parents. Adherence to therapy will be stimulated by the required completion of bladder diaries and the active encouragement of the participant and parent by the physiotherapist during the 6-weekly follow-up visits. During the follow-up visits, the potential progression of symptoms will be actively evaluated by going through the completed diaries, together with the participant.

To check the adherence to the treatment protocol by the participant, registration of the performance and duration of daily TENS-application in a diary will be requested.

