## Data collection and management

### Plans for assessment and collection of outcomes {18a}

Bladder diaries and the parents reported satisfaction of urinary symptoms questionnaire are distributed at the beginning of treatment on paper. The demographic data from each participant will be derived from the electronic medical record (EMR). All outcome data will be collected at the end of the 12 weeks treatment period and converted by the research assistant into a digital file. A standard frequency-volume chart with additional information of urinary incontinence episodes and urgency episodes will be used as bladder diary [10]. The parents’ reported satisfaction of urinary symptoms score is a non-validated 7 points Likert scale.

The following case report forms will be collected (see also Fig. 3 and Table 1):
-t1: First visit with the PS.

CRF with baseline patient characteristics: age, gender, presence of daytime urinary incontinence and/or enuresis nocturna, and comorbidities.

CRF with technical investigations: presence of urinary tract infection (yes/no), kidney ultrasound (US) (normal or abnormal), PVR on bladder US (ml), cystometric bladder capacity at uroflowmetry, and staccato pattern on uroflow suggestive for dysfunctional voiding (Y/N).

0: Second visit with the PS.

CRF with baseline daytime and nighttime diary parameters (volume intake, daytime diuresis, micturition frequency, AVV during the day, urgency episode (Y/N), number of urinary incontinence episodes, N of defecations, N of wet nights, nocturnal urine production, netto urine loss/night, presence of nocturnal polyuria), and parents’ reported satisfaction of urinary symptoms.

t1: First visit with the PT.

CRF with patient number, allocation group.

t2: Second visit with the PT, 6 weeks after ambulant treatment.

CRF with daytime and nighttime diary parameters after 6 weeks of treatment (same parameters as at visit 2 + averaged volume of 3 supervoids at 6 weeks) and parents reported satisfaction of urinary symptoms.

CRF with recorded (serious) adverse effects: the adverse event form.

*t3: Third and last visit with the PT, 12 weeks after ambulant therapy.

Same CRF’s as in t2.

CRF with treatment response (non-responder, partial responder, complete responder).

*t4: Third visit with the PT.

Same CRF’s as in t2.

CRF with the maintenance of treatment effect in partial and complete responders (in weeks).

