### Adverse event reporting and harms {22}

During each follow-up visit, the physiotherapist will query the participant for adverse events. In case adverse events occur during ambulant therapy, participants are asked to contact the physiotherapist. This information will be briefed to the CI, who will include all the details (time of occurrence, severity and attribution of the event—related or non-related to the therapy) on the adverse events form. AE will be quarterly reported to the Ethical Board or the Ghent University.

Adverse events will be treated along the standard of care.

Serious adverse events (SAE), also reported on the Adverse Event form, will be immediately (within 24 h) reported by the CI to the sponsor, the Ethical Board, and the FAGG (Federal Agency of Medicines and Health products). In case of any unexpected SEA of SUDA (serious adverse device effect), the study will be stopped. However, there are no SEA to be expected from TTNS, as previous studies in adults have proven its safety [3].

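### Blinding only partly protects the AVV comparison: the unblinded physiotherapist coaches families, reviews their diaries and hosts the visit where the 12-week outcome is collected

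*Protocol article*

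**What the plan says.** Trial design {8} calls the study a "single-center randomized controlled double-blinded trial". Who will be blinded {17a} gives the roles: "The treatment is blinded for the patient, the parent, the treating PS, and the research assistant", followed by "The physiotherapist is the only unblinded party". Concealment mechanism {16b} confirms that the physiotherapist sees the allocation sequence and assigns the treatment.

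The same person's visits carry most of the contact with families:

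- **Urotherapy.** Study schedule places it at the first physiotherapist visit. The Urotherapy section adds follow-up at weeks 6 and 12. It includes holding exercises three times a week, with the delay gradually lengthened.
- **Encouragement.** Strategies to improve adherence {11c} relies on "the active encouragement of the participant and parent by the physiotherapist during the 6-weekly follow-up visits".
- **Diary review.** Study schedule and {11c} have the completed diaries gone through with the family at these visits.
- **Outcome collection.** In describing the third physiotherapist visit, at 12 weeks, Study schedule says: "Primary outcomes are collected and delivered to the research assistant". Plans for assessment {18a} lists the response form for the same visit.
- **Adverse events.** Section {22} says that at each follow-up visit "the physiotherapist will query the participant for adverse events".

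On the protective side, {16b} and {18a} have a blinded research assistant digitise and analyse the data. The Sham group section checks family blinding by asking parent and child to guess their arm.

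**The concern.** AVV comes from a diary kept at home, and it plausibly responds to effort. A child who is coached harder to delay voiding may pass larger volumes whether or not current is delivered. If the coach knows the arm and coaches even slightly differently, the difference appears in the primary contrast as if stimulation had caused it. Blinded digitisation cannot detect this, because the difference arises before the diary is written.

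A second route is the handling of the diary. If the 12-week diary passes through the physiotherapist's review before it reaches the assistant, someone who knows the arm has discussed it with the family first. Adverse-event questions are open to the same difference in emphasis.

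The Background itself cites an earlier sham trial as showing how strong the placebo response to any management can be in these children. Under Dissemination plans {31a}, a positive part I launches part II, so a false positive would have consequences.

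**Working it through.** **1. Who can influence what, and when**

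| Step | Who is present | Blinded? | Route for bias |
|---|---|---|---|
| Urotherapy and encouragement, first visit and week 6 | Physiotherapist, family | Family yes, physiotherapist no | Effort and technique before the 12-week diary |
| Recording the 12-week diary | Family | Yes | Only through earlier coaching |
| Review and collection, week 12 | Physiotherapist (implied), family | Family yes, physiotherapist no | Handling or discussion of a completed diary |
| Digitising and analysis | Research assistant | Yes | None apparent |
| Adverse-event questions | Physiotherapist | No | Emphasis in the questioning |

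Two steps are exposed for AVV: coaching at the first two visits, and handling at the third. Encouragement at week 12 cannot change volumes that are already recorded.

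**2. Inputs**

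From Sample size {14}: SD 20 percentage points, 12 per arm, two-sided 5%, assumed effect 20 points. From Statistical methods {20a}: Mann-Whitney U test. The bias sizes are my assumption; the article gives none.

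**3. The plan's own figure**

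For a difference of 20 and SD 20, n per arm = 2 × (1.960 + 0.842)² × (20/20)² = 15.7, so 16 per arm, not 12. That is a separate matter and this point does not rest on it. I use the stated 12.

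**4. Effect of an assumed bias when there is no true effect**

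Standard error of the difference = 20 × √(2/12) = 8.16 points. For a bias b favouring TTNS, the shift is s = b/8.16, and the two-sided rejection rate by the normal approximation is Φ(s − 1.96) + Φ(−s − 1.96). For b = 5: s = 0.612, giving Φ(−1.348) + Φ(−2.572) = 0.089 + 0.005 = 9.4%.

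The planned test was simulated with exact Mann-Whitney p-values, normal data and 20,000 runs (simulation error about 0.3 points or less):

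| Assumed bias (points) | s | Normal approximation | Mann-Whitney, 12 per arm |
|---|---|---|---|
| 0 | 0 | 5.0% | 4.4% |
| 2 | 0.245 | 5.7% | 5.1% |
| 5 | 0.612 | 9.4% | 8.3% |
| 8 | 0.980 | 16.5% | 13.6% |
| 10 | 1.225 | 23.2% | 19.6% |

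The Mann-Whitney column is the relevant one. A bias of a quarter of the assumed effect (5/20) roughly doubles the false-positive rate, and a bias of half (10/20) raises it more than fourfold. A bias of 2 points hardly matters. At 16 per arm the Mann-Whitney rates are 4.6%, 9.6% and 25.8% for 0, 5 and 10 points, so a larger sample does not remove the problem.

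**The case against.** The strongest reply is that the endpoint has a blinded chain. Families measure and write down the volumes, are told that they cannot infer their arm, and have their guess checked. The assistant does not know the participant number, the allocation or the meaning of groups A and B. Every child is to receive the same standard urotherapy, and its components are itemised. Someone must set the sham dial, so one unblinded person is hard to avoid, and the article discloses this openly. The assumed biases are hypothetical in both size and direction.

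Most of this stands, and it rules out several stronger readings that a reader might infer:

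- **That blinding gives no protection.** It does: recording, digitising and analysis are all in blinded hands.
- **That the physiotherapist corrects diaries.** The article describes only a review of completed diaries.
- **That the physiotherapist is stated to collect the outcome and fill in the response form.** The collection sentence names no one, and {18a} lists forms by visit without saying who completes them. Response is also arithmetic on AVV with fixed cut-offs, which leaves little room for judgement.
- **That calling the trial double-blinded is a contradiction.** Section {17a} lists the blinded roles and the exception, so the label is loose rather than false.
- **That adverse-event assessment rests wholly with the physiotherapist.** The physiotherapist asks, but the chief investigator enters severity and attribution.

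The coaching route remains. A statement that urotherapy is the same in both arms gives an intention. The article describes nothing that holds encouragement or diary review constant when the person giving it knows the arm. The blinding check asks families what they guessed, so it would not detect different coaching of families who stayed blinded.

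**Conclusion.** The point holds as a residual risk of performance bias, with some risk in outcome handling. Blinding of families and of the assistant does not fully protect the AVV comparison, because the one person who knows the arm hosts the coaching and diary-review visits and, by implication, the visit at which the 12-week outcome is collected.

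The documents do not allow the bias to be sized, and nothing in them shows that one has occurred. The illustration of about 8% at 5 points and 20% at 10 points, against 4.4% with none, assumes normal data with SD 20, 12 per arm, no true effect and a constant shift favouring TTNS. A shift the other way, for example extra encouragement for sham children, would hide a real effect instead. The weakness does not invalidate the trial, but it can be reduced cheaply.

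**What to change.** - **Study schedule and {18a}:** families return the completed 12-week outcome diary and the parent satisfaction score in a sealed envelope, marked only with the pseudonymous code, to the blinded research assistant before the 12-week review with the physiotherapist. The research assistant alone derives AVV and the response category.
- **Urotherapy section and {11c}:** the physiotherapist continues to give urotherapy and the 6-week review, using one fixed script for both arms. The content of urotherapy is unchanged. Instructions about the device already differ by arm and lie outside the script.
- **Section {22}:** adverse events are asked about with one fixed set of questions in both arms. The research assistant should not ask about sensation: active-arm families adjust to a felt stimulus and sham families feel none, so the answers could unblind the person who analyses the data.
- **Discussion:** state the remaining performance-bias risk from the unblinded physiotherapist as a limitation.

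The cost is a short amendment and slightly more research assistant time, with no new staff. Recruitment was still open at publication, so the change would fall partway through. Its date should be recorded, and the report should say how many participants were handled under each procedure. The sealed return reduces the handling risk at week 12; the script reduces the coaching risk but cannot remove it.

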### Procedure for unblinding if needed {17b}

In case the participant and parent want to discontinue with the trial, the allocated intervention will be revealed. In no other circumstances, unblinding is allowed. The treating PS will be unblinded before the last follow-up visit at 18 weeks. The research assistant will be unblinded after all data has been entered into the database.

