### Composition of the data monitoring committee, its role and reporting structure {21a}

Since previous trials have been conducted with TTNS in children showing no serious adverse events [5], there is no formal appointed independent data monitoring committee. Any potential harm or risk to the patients will be assessed by a section of the HIRUZ clinical trial unit. This section has no conflict of interests in the trial or medical device company. In case of any risk to the patient’s safety, the chief investigator, sponsor of the trial and ethical board will be informed. Dependent from the severity of the AE, the decision to prematurely stop the clinical trial will be taken.

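### The unblinding rule makes no exception for a serious adverse event, so device relatedness is, by implication, judged without the child's allocation

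*Protocol article*

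**What the plan says.** **Unblinding (Protocol article, Procedure for unblinding if needed {17b}).** The one unscheduled trigger is withdrawal: "In case the participant and parent want to discontinue with the trial, the allocated intervention will be revealed". The next sentence closes the list: "In no other circumstances, unblinding is allowed". The remaining releases are scheduled. The treating specialist is told before the 18-week visit and the research assistant after data entry. Under Study schedule, the family is told at the 18-week visit.

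**Who knows the arm (Who will be blinded {17a}).** "The physiotherapist is the only unblinded party".

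**Safety flow (Adverse event reporting and harms {22}).** The physiotherapist collects events: "During each follow-up visit, the physiotherapist will query the participant for adverse events". Then "This information will be briefed to the CI", and the chief investigator records timing, severity and whether the event is attributed to the therapy. Serious events "will be immediately (within 24 h) reported by the CI to the sponsor, the Ethical Board, and the FAGG". The section also sets a stop: "In case of any unexpected SEA of SUDA (serious adverse device effect), the study will be stopped". It adds that no serious events are expected from the treatment.

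**Oversight (Composition of the data monitoring committee {21a}).** There is no independent committee. Instead, "Any potential harm or risk to the patients will be assessed by a section of the HIRUZ clinical trial unit". This section makes an early stop depend on the severity of the event.

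**Sham (Intervention description {11a}).** Sham children use the same device and electrode positions, at a setting that delivers no current.

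**The concern.** A section on unblinding if needed would normally provide for a serious safety event. This one excludes it in terms. That is a stated rule and not something a condensed article has merely left out: a fuller protocol could add the exception only by contradicting the sentence.

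The rule matters here because the arms differ in whether the stimulator delivers current. If a serious event occurs, a natural question for anyone judging device relatedness is whether this child was meant to be stimulated. The physiotherapist knows the answer, but the plan gives no permission to pass it to those who assess harm. The participants are children aged 5 to 12 who use the device at home for an hour a day, and the protocol has replaced a monitoring committee with a section of the clinical trial unit. That section should be able to obtain the allocation when it needs it.

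**Working it through.** The plan gives no figure on this point, so the check sets the sections side by side.

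1. **Is a serious event a permitted reason to unblind?** Section {17b} allows one unscheduled reason, the family's wish to discontinue, and forbids all others. The scheduled releases come at the 18-week visit or after data entry. A serious event in, say, week 5 fits none of these. If the family then chooses to leave, the allocation is revealed, but that depends on the family's choice, and the text does not say that the safety assessor is told.

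2. **Does whoever judges relatedness know the arm?** Section {22} gives the attribution to the chief investigator. Section {17a} does not list the chief investigator among the blinded parties, but says that the physiotherapist alone is unblinded. Confidentiality {27} opens the database to the chief investigator only at the end of the study. The physiotherapist briefs the chief investigator on events, and the text does not say what the briefing contains. Including the allocation would conflict with {17a} and {17b}. Blinded attribution is therefore an implication, though it is the only reading that complies with both sections.

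3. **Does the arm bear on the judgement?** Yes, because the sham setting delivers no current. It does not settle the judgement (see the objection).

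4. **Which parts of the stopping rule are affected?** Section {22} is read here as naming two triggers: an unexpected serious adverse event, or a serious adverse device effect.
   - *Unexpected serious event.* The protocol expects none, so on its own terms every serious event is unexpected. This trigger operates in either arm and whatever the relatedness. Blinding does not affect it.
   - *Serious adverse device effect.* This requires a judgement about the device, so it is made without the allocation.
   - *Severity-dependent decision in {21a}.* The text states no condition on relatedness or arm. It is worded differently from {22}, where the stop is automatic.

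5. **What would disclosing one allocation leak?** Sequence generation {16a} uses blocks of 4 at 1:1, so each block holds 2 children per arm. Before disclosure, another child in the block has a chance of 2/4 = 1/2 of being on active treatment. If one child is disclosed as active, 1 active place is left among 3, so the chance is 1/3. If one is disclosed as sham, it is 2/3. Two disclosures of the same arm in one block would fix the other two. This applies only to someone who knows which children share a block.

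**The case against.** **The stop does not depend on the arm.** A reader might infer that an event in a sham child, wrongly labelled as device-related, could stop the trial in error. The documents do not support that. Section {22} also stops the study for any unexpected serious event and expects none, so the same event would trigger the stop if labelled unrelated. This objection stands, and it confines the point to the relatedness judgement and the device-effect trigger.

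**Allocation is not decisive.** The only adverse reaction the protocol names is a skin reaction to the adhesive electrodes. Sham children wear these too, so a true device effect can occur without current. Sham families also hold a working device and are only discouraged from turning it up. This stands: allocation is relevant evidence, but it is not the whole answer.

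**Blinded attribution by an investigator is ordinary practice.** It is. The defect is the absolute bar, which leaves nobody charged with assessing harm a permitted way to learn the arm.

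**The trial unit section may receive events by another route.** A reader might infer from its absence among the recipients in {22} that it is told nothing. The text does not establish this. Section {21a} presupposes that events reach it, the list in {22} is not said to be exhaustive, and a condensed article may leave an internal route to the full protocol. Nor is it the only outside check, since the Ethical Board and the federal agency also receive serious events. The missing recipient is a separate matter and does not cause the blinded judgement.

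**Conclusion.** The concern holds in a limited form. As written, {17b} excludes a serious adverse event as a reason to unblind. By implication from {17a}, the attribution to therapy and the device-effect trigger in {22} are judged without an allocation that bears on whether current was delivered. The trigger for any unexpected serious event is unaffected.

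No numerical size can be given. The protocol states no background rate of serious events. A rate assumed from outside would give the chance that some event occurs, not the chance that one is misattributed. The point leaves the primary comparison untouched. It deserves a change because the participants are children, there is no monitoring committee, and the remedy is small.

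The verdict rests on two readings: that the statement about the sole unblinded party covers the chief investigator and the trial unit section, and that the stopping sentence in {22} names two alternative triggers.

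Two further places need reconciling, whatever is decided on unblinding: whether the trial unit section receives serious-event reports ({21a} against {22}), and whether a stop depends on severity ({21a}) or is automatic ({22}). Which stopping rule applies is for the sponsor to settle.

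**What to change.** **Section {17b}:** add one permitted circumstance. For a serious adverse event, the physiotherapist may disclose that child's allocation to the HIRUZ section that {21a} charges with assessing harm. The family, the treating specialist and the research assistant stay blinded. The chief investigator's own attribution can also remain blinded.

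**Sections {21a} and {22}:** state whether the HIRUZ section receives serious-event reports, and bring the two stopping statements into agreement.

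**Cost:** one added sentence and a short reconciliation in a protocol amendment. No new staff are needed, because the unblinded physiotherapist and the HIRUZ section already exist. The downside is that, with blocks of 4, a disclosed allocation can help the person told to infer others in the block. That is tolerable because disclosure is limited to a section with no stated role in enrolment, treatment or outcome data. Routine listings of adverse events by arm are not needed to resolve this point.

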#### Sham group

The same TENS device, electrode positioning, pulse frequency (20 Hz) and pulse width (200 μs) as in the intervention group are applied for the sham group. Unlike the intervention arm, the pulse intensity button is set on position number “1,” which is the test button on which no electric current is delivered. Parent and child are told that subsensory stimulation will be delivered, not affecting the outcome as proven earlier in other types of neuromodulation trials [12]. In this way, we counter their worry that no sensation is felt. To discourage children or parents from exceeding number 1, they are told higher stimulations can affect the result of treatment in a negative way.

The same stimulation protocol as for the intervention group (1 h daily during 2 periods of 6 weeks) needs to be followed at home after the first visit. When switching the TENS-device on, they may not exceed number 1. This way, no current is supplied.

To check whether this method of blinding was successful, at the end of the trial, both parent and child are asked to indicate to which group they think they belonged.

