**Table 1 Tab1:**
[figure not shown]
Schedule of enrolment, interventions and assessments

To evaluate the duration of clinical response, a third period of 6 weeks without any treatment (the observation period) is inserted. During this “wash-out” period, the same set of bladder diaries must be completed.

The study is closed at the end of the last follow-up visit at 18 weeks at the treating PS (t_4_). The PS will be briefed beforehand to which treatment arm the participant was allocated. The same assessment as during baseline will be repeated and the parent and participant will be unblinded during this follow-up visit.

For post-trial care, see item 30.

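### The analyst's unblinding is tied to data entry rather than to a completed analysis, and the specialist learns the arm before the 18-week records are made

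*Protocol article*

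**What the plan says.** **The analyst.** Concealment mechanism {16b} describes the person who does the analysis as blinded: "The research assistant, however, who analyzes all the data, is neither aware of the participant number, the group allocation per participant", nor which treatment A and B stand for. Who will be blinded {17a} also lists the research assistant among the blinded parties and names the physiotherapist as the only unblinded one. Procedure for unblinding {17b} then sets the moment of disclosure: "The research assistant will be unblinded after all data has been entered into the database".

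**The treating specialist.** {17a} lists the treating pediatric specialist (PS) as blinded. {17b} says: "The treating PS will be unblinded before the last follow-up visit at 18 weeks". The text after Table 1, under Study schedule, says the same: "The PS will be briefed beforehand to which treatment arm the participant was allocated". It continues: "The same assessment as during baseline will be repeated and the parent and participant will be unblinded during this follow-up visit".

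**The forms.** Plans for assessment and collection of outcomes {18a} labels the 18-week contact "t4: Third visit with the PT". It repeats the t2 forms there, which include diary parameters and the parents' satisfaction score, and adds a form for how many weeks the response was maintained. The form at the first physiotherapy visit (t1) carries the patient number and the allocation group.

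**The blinding check.** Under Sham group: "at the end of the trial, both parent and child are asked to indicate to which group they think they belonged".

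**The concern.** Two people whose blinding the article relies on can learn the allocation before their work is finished.

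For the research assistant, the only stated condition is that the data are in the database. The step that normally follows is the analysis, which this same person carries out. If the code is released then, choices that depend on the data could be made with the arms in view. In a trial of 24 children such choices can shift a result.

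For the specialist there is nothing to infer: the arm is disclosed before the visit at which the examinations are repeated and the last forms collected. Satisfaction is a subjective rating, and deciding for how many weeks a response lasted is a classification. Both are better recorded before anyone in the room knows the arm.

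The blinding check is exposed in a similar way, because the study closes at the visit where the family is told the allocation. The check matters here: sham delivers no current, whereas active stimulation is raised until it is felt.

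**Working it through.** The protocol gives no figure on this point and none is needed. The check sets the sections side by side.

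**1. When may the analyst learn the arms?**
- {16b}: the analyst does not know the participant number, the allocation or the identity of A and B.
- {17b}: the analyst is unblinded after data entry. Neither lock nor completed analysis is mentioned.
- Read together, {17b} gives an earliest moment. Unblinding after the analysis would satisfy both sections; unblinding between entry and analysis would satisfy {17b} and contradict {16b}. The wording permits the second.
- {17b} also restricts unblinding to families who discontinue, excludes every other circumstance, and then lists two more unblindings.
- The t1 form in {18a} holds the two items that {16b} says the research assistant must not know. {18a} also has this person convert the outcome data into a digital file. Nothing says that the t1 form is kept apart.

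**2. What is still open once the data are entered?**
- Imputation depends on a missing-value analysis and is followed by a sensitivity analysis of unstated form ({20c}).
- The per-protocol analysis is run if non-adherence is noticed, with no threshold given ({20c}).
- A regression on fluid intake may be performed if a prior test is significant ({20b}).
- Not open: the between-arm test, fixed as Mann-Whitney ({20a}).

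**3. Is a masked analysis available?** Yes. Sequence generation {16a} uses labels A and B, and the physiotherapist decided which is which. The two-sided between-arm test can be run on those labels.

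**4. Which outcomes does the specialist's unblinding reach?**
- The Outcomes section has six headed outcomes: one primary and five secondary. Five are changes from baseline to week 12 (average voided volume, supervoid volume, incontinence episodes, voiding frequency, parent satisfaction). The specialist is told just before week 18, which is 18 − 12 = 6 weeks later, so these five are out of reach.
- The sixth, duration of effect, rests on weekly diaries in weeks 12 to 18. The family is told during the 18-week visit, so these diaries are kept blind.
- What remains is whatever is recorded or classified at t4: the repeated examinations, the 18-week satisfaction score and the weeks of maintained response.

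**5. Who conducts t4?** Study schedule places it with the treating PS; {18a} says PT. The same list in {18a} calls t3 the last visit with the PT, so PT at t4 is probably a slip. On either reading the staff member knows the arm.

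**6. When is the blinding question asked?** It is set for the end of the trial. The study closes at the 18-week visit, which is also where the reveal happens, and no order between the two is given.

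**The case against.** The strongest reply is that {17b} and {16b} can be read together, and that the order of lock, analysis and code release is commonly left to an analysis plan or full protocol, neither of which is shown. This stands in part. A reader might infer that the analyst is unblinded before the analysis, but the article does not say so. What it does is choose a trigger, data entry, that fails to secure what {16b} describes.

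Second, the analyst's freedom is limited: the test is fixed and the per-protocol analysis is additional to intention-to-treat. That is fair and keeps the point modest. The choices listed above remain.

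Third, a reader might infer that the evidence on whether the effect lasts is unblinded altogether. The documents do not support this, because the home diaries precede the family's unblinding. Only their final recording and classification at t4 are exposed.

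Fourth, a reader might infer that specialists, who also recruit, could use disclosed arms and the blocks of 4 to predict later allocations. The documents do not carry this far. {16a} gives the list to the physiotherapist, appointment order sets the sequence ({16c}), and several specialists in two departments recruit. Nothing shows that a specialist would know which children share a block. Re-ordering the 18-week visit would not change what recruiters learn in any case.

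Fifth, the 18-week reveal has a purpose: sham participants without success may enter part II, and further care is chosen then. This stands, so the reveal should stay at that visit and only its place within the visit should move.

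Finally, nothing says that the blinding question follows the reveal, and at 12 weeks it would be asked at a visit with the unblinded physiotherapist. Both remarks are correct. The essential requirement is that it comes before any disclosure; 12 weeks is preferable because the primary outcome is collected then.

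**Conclusion.** The point holds in a limited form. The analyst's unblinding trigger is too early or, at best, ambiguous, and it needs reconciling with {16b}. The specialist's unblinding before the 18-week assessment is explicit in two places.

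The specialist's unblinding leaves the 12-week primary outcome and the four 12-week secondary outcomes untouched. It exposes the repeated examinations, the t4 satisfaction score and the maintenance classification for every child who attends at 18 weeks. The analyst's trigger could touch any outcome, but only through the choices left open and only if the code is in fact released before the analysis. No bias can be quantified from the documents.

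The verdict assumes that the research assistant performs the analysis, as {16b} states, and that no unshown document already fixes a later code release.

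**What to change.** 1. **{17b}, analyst.** State that the research assistant analyses the groups as A and B and receives the code only after the database is locked and the planned primary and secondary analyses have been run. Withhold the allocation field of the t1 form from this person until then. Reword the sentence limiting unblinding to discontinuation so that it agrees with the planned disclosures.
2. **Study schedule and {17b}, 18-week visit.** State that the 18-week diaries, satisfaction score, examinations and maintenance classification are completed and signed before the specialist and the family are told the arm. Keep the reveal at that visit, for post-trial care and part II eligibility.
3. **Sham group, blinding question.** Ask it before any reveal, preferably at the 12-week visit (t3).
4. **{18a} and Study schedule.** Reconcile who conducts t4, the PT or the PS.

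The cost is a change of wording and of the order of existing steps. Sample size, power and significance level are unchanged, and no visit or person is added.
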